## Introduction

The World Hip Trauma Evaluation (WHiTE) project was set up to measure outcome in a comprehensive cohort of UK patients with hip fracture. All patients in the cohort are treated under a single comprehensive treatment pathway. A core outcome set, including health-related quality of life (QoL), is collected on all the patients.

This protocol describes the current multicentre project that will be used as a vehicle to deliver a series of embedded observational studies.

Osteoporotic hip fractures present a significant global challenge to patients, clinicians and healthcare systems. It is estimated that hip fracture accounts for 1.4% of total social and healthcare costs in the established market economies.^1^ Approximately 8.5% of patients with hip fracture will die within 30 days of injury^2^ and 22.5% within 12 months.^2^
^3^ In addition, the majority of survivors experience a significant reduction in health-related QoL.^4^
^5^ The challenge is expected to intensify with a rise from the 1.3 million hip fractures in 1990 to 6.3 million globally by 2050.^6^

The National Hip Fracture Database (NHFD) already captures data on almost all patients with hip fracture in England, Wales and Northern Ireland.^7^ Although it is used principally for national clinical audit, there is considerable potential to use the NHFD for research purposes.^3^ However, the NHFD does not routinely capture patient-reported outcome measures and there is substantial variation in clinical decision-making (eg, choice of fixation device) between hospitals and individual surgeons, which risks introducing confounding to observational studies embedded within the NHFD.^8^

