### Consent

Patients with a hip fracture are a clinical priority for urgent operative care and will usually undergo surgery on the next available trauma operating list. All WHiTE recruiting sites treat hip fracture patients according to national guidelines and so patients will be managed according to a series of common standard treatment pathways. The WHiTE study will not affect their treatment in any way. The patients will be approached for consent to be part of this cohort study in the immediate postoperative period.

At the first appropriate time when the patient has regained capacity (usually the first day after surgery) a research associate will provide the participant with the study information. The patient will be given the opportunity to ask questions and discuss the study with their family and carers for as long as they require. They will then be asked to provide written consent to participate in the study. If the patient does not wish to complete questionnaires for the study at this stage, they will be asked if they are happy to provide written consent for us to access and use any routine NHS data, including that collected through the NHFD. Alternatively the patient can choose to decline to have any data entered into the study.

Best efforts will be made to involve participants who, temporarily or permanently, lack capacity in the decision to be involved in the study. The clinical team will make a judgement about the amount and complexity of the information that the participant is able to understand and retain on an individual basis. Appropriate information will be communicated to the participant and updated as their understanding changes. In the event that a patient has temporary loss of capacity, we will follow best practice and ask the patient for consent as soon as they are able to do so.

In accordance with section 32 subsection 9b of the Mental Capacity Act 2005, where a patient does not have capacity to consent for themselves, we will seek agreement from an appropriate consultee.

Where a personal consultee is available, they will be provided with the study information. The personal consultee will be given the opportunity to ask questions and discuss the study after which they will be asked to provide agreement, which will be documented. The personal consultee will complete the outcome questionnaires on behalf of the patient.

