### Sample size

A sample size for a study such as the one we propose here is difficult to determine with any degree of precision. This is, in large part, due to the flexibility of the approach being adopted, that is, specific research questions will be identified by the Oversight Committee over time.

However, there are aspects that are determined a priori that can guide an initial sample size. A key determinant of the sample size, and also an important outcome in itself, in this frail (elderly) population is the death rate. Previous analyses^5^
^13^ have shown that the death rate in this group is between 20% and 30% at 12 months, but data were sparse and limited. One research question that we know will be important is to establish the overall population death rate and model how it changes in the immediate postoperative period. Table 1 shows 95% CIs for estimates of death rates of 20% and 30% for varying sample sizes (n), based on a binomial model.

**Table 1 BMJOPEN2016011679TB1:** CIs (95%) for death rates of 20% and 30% by sample size (n)

	Death rate	
n	20%	30%
100	(12.9 to 29.4)	(21.5 to 40.1)
300	(15.7 to 25.1)	(24.9 to 35.6)
1000	(17.6 to 22.6)	(27.2 to 33.0)
3000	(18.6 to 21.5)	(28.4 to 31.7)
6000	(19.0 to 21.0)	(28.8 to 31.2)

In order to estimate the death rate to a high level of precision (within 1%), a reasonable target overall sample size is therefore ∼6000 participants. The death rate is likely to vary within important subgroups of the population (eg, fracture type), so it is also important to consider the precision of estimation of the death rate within the smallest clinically important subgroup, which we think is likely to be in the order of 5% of the overall population. Based on 6000 participants, this amounts to a subgroup of 300, and a CI of ∼10% for estimating the death rate.

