It is anticipated that the data generated by the cohort study will be used to support and inform hypotheses that are suggested by clinical practice. The Oversight Committee will decide whether any interim analyses are necessary to inform future questions in order to prevent repeated attempts to interrogate the data set without a priori hypotheses. The cohort study data will also be used to update estimates of ‘nuisance’ parameters, such as the death rate and QoL variability in the study population. These nuisance parameters will be used to refine estimates of sample sizes for future embedded randomised controlled trials.

An example observational study within the WHiTE observational cohort might investigate whether the type of fracture a patient sustains influences the patient's outcome. While the optimal interventions for each fracture pattern are defined in current guidelines, the effect of fracture pattern on patient outcome is not well understood. Data from the NHFD 2014 report (n=64 838) give a breakdown of fracture types as follows: undisplaced intracapsular 9.5% (n=6165), displaced intracapsular 48.8% (n=31 656), trochanteric 34.6% (n=22 422), subtrochanteric 5.4% (n=3507) and not specified 1.7% (n=1088). Suppose we were interested in understanding the relationship between the type of intervention, anaethestic and rehabilitation within the subtrochanteric fracture subgroup. This subgroup comprises ∼5.4% (n=325) of the study population (n=6000). Let us assume 90% follow-up rates at 4 months (ie, n is ∼300), with EQ-5D as the primary outcome, and the definitive analysis is a multiple linear regression adjusting for age and gender as minimum. Taking a conservative estimate of R2^5^
^13^ to give a value of Cohen's f^2^ of 0.05, suggests that we will have 85% power to detect a statistically significant regression analysis, at the 5% level, in the smallest subgroup of interest (subtrochanteric fractures) for a sample size of 300 patients. A 4-month follow-up rate of >90% is anticipated based on a WHiTE pilot study, which successfully followed up 88% of patients at 12 months.^5^

Analogous economic burden and health economic assessments will be integrated into the analysis plan for each observational study. The economic assessments will be conducted from the recommended NHS and personal social services perspective.

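### The example power calculation for EQ-5D in subtrochanteric fractures deducts for non-response but not for death, so its sample of about 300 and its 85% power are too high

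*Protocol article*

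**What the plan says.** All of the power statements are in the Sample size section of the protocol article.

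- **Subgroup size.** The share comes from the national database report ("subtrochanteric 5.4% (n=3507" of 64 838) and is carried to the cohort: "This subgroup comprises ∼5.4% (n=325) of the study population (n=6000").
- **Analysis sample.** The text continues: "Let us assume 90% follow-up rates at 4 months (ie, n is ∼300), with EQ-5D as the primary outcome". For 300 patients and f² = 0.05 it states 85% power at the 5% level. The model adjusts at least for age and gender; its degrees of freedom are not given.
- **Basis for the rate.** "A 4-month follow-up rate of >90% is anticipated based on a WHiTE pilot study, which successfully followed up 88% of patients at 12 months".
- **General subgroup statement.** Earlier in the section, a subgroup of 300, which is 5% of 6000 participants, is said to give 95% power at f² = 0.08 and 75% at f² = 0.05 with 10 degrees of freedom. A later sentence says power stays above 80% if the model explains 10% of the variance, even with some unquantified reduction for loss to follow-up.
- **Mortality.** The Introduction says: "Approximately 8.5% of patients with hip fracture will die within 30 days of injury", and gives 22.5% within 12 months. The Sample size section says "the death rate in this group is between 20% and 30% at 12 months".
- **How death is recorded.** The Outcome data section lists death as one of the possible residential statuses at 4 months.

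**The concern.** A patient who has died by 4 months has no EQ-5D questionnaire, and the article gives no rule for scoring one. The step from 325 to about 300 uses the follow-up rate alone, so it amounts to assuming that 90% of everyone enrolled supplies an EQ-5D score.

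The pilot figure cannot support that assumption. If 20–30% are dead at 12 months, 88% of all enrolled patients cannot have returned a 12-month EQ-5D. The article cites the same pilot reference for the 88% and, with one other, for the 20–30%. The 88% therefore either includes deaths as known outcomes or has survivors as its denominator. In neither case is it an EQ-5D completion rate among all enrolled.

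At stake is the power printed for the smallest subgroup of interest. Embedded EQ-5D studies planned from this figure would count on patients who cannot have the outcome.

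**Working it through.** **Method.** Overall F test of a multiple regression with u model degrees of freedom and n − u − 1 error degrees of freedom. Power is the upper tail of the noncentral F with noncentrality f² × n, at the 5% level.

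**1. Reproducing the stated figures**

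- Subgroup: 3507 / 64 838 × 6000 = 324.5, stated as 325. Then 325 × 0.90 = 292.5, stated as about 300.
- Example, n = 300, f² = 0.05: u = 4 gives 88.6%, u = 5 gives 85.9%, u = 6 gives 83.4%, u = 7 gives 81.0%. The stated 85% therefore fits u = 5 or 6. That is an inference. Five would match one term each for age, gender, intervention, anaesthetic and rehabilitation.
- General statement, n = 300, u = 10: 93.8% at f² = 0.08 (stated 95%) and 74.3% at f² = 0.05 (stated 75%). Both are sound for 300 analysed patients.

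**2. What 90% of all enrolled would require**

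If only 8.5% had died by 4 months, the response needed among survivors is 0.90 / (1 − 0.085) = 98.4%. Above 10% mortality, 90% of all enrolled cannot be reached.

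**3. Deducting deaths**

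Records = enrolled × (1 − mortality at 4 months) × 0.90. The assumptions are mortality between 8.5% and 22.5% and 90% response among survivors.

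- 325 × 0.915 × 0.90 = 267.6, about 268
- 325 × 0.775 × 0.90 = 226.7, about 227

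If the 90% instead counts the dead as followed up, deaths come off the 292.5: 292.5 − 27.6 = 265 and 292.5 − 73.1 = 219, which is slightly worse.

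**4. Power in the example at f² = 0.05 (stated: 85%)**

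| Analysed n | u = 5 | u = 6 |
|---|---|---|
| 300 | 85.9% | 83.4% |
| 268 | 81.0% | 78.1% |
| 227 | 72.9% | 69.5% |

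With u = 5, 85% power needs 294 analysed patients. Equivalently, 85% power is reached at f² of about 0.055 with n = 268 and about 0.065 with n = 227.

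**5. The general statement, starting from 300 enrolled (u = 10)**

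300 × 0.915 × 0.90 = 247 and 300 × 0.775 × 0.90 = 209.

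| Analysed n | f² = 0.08 (stated 95%) | f² = 0.05 (stated 75%) | R² = 10%, f² = 0.111 (stated >80%) |
|---|---|---|---|
| 247 | 87.1% | 63.4% | 96.6% |
| 209 | 79.2% | 54.2% | 92.5% |

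The last column still supports the article's claim.

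**The case against.** The strongest reply is that little depends on this example. It is introduced as hypothetical, each real study needs approval by the Oversight Committee, and the 6000 target rests on the precision of the death rate, where deaths are the outcome and not a loss. The broader conclusion of good power for small to moderate effects also largely holds: the f² detectable with 85% power stays within the article's 0.05–0.08 band. All of this stands and limits the severity. It does not make the printed 85% correct for 325 enrolled patients.

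The size of the shortfall is also uncertain:

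- The low end, 227, applies 12-month mortality to a 4-month outcome and is a bound, not an expectation.
- Both mortality figures are for all hip fractures, not subtrochanteric ones.
- The 8.5% runs from injury, whereas consent is sought after surgery, so deaths before consent never enter the cohort and true early mortality among participants may be somewhat lower. Even at an assumed 5%, 325 × 0.95 × 0.90 = 278, and power with u = 5 is about 83%.

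Scoring deaths as 0 on the utility scale would keep n near 292 (84.8% with u = 5). The article does not say this will be done, and it would change what is being estimated.

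A reader might infer three stronger points that the article does not support:

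- **That the 95% and 75% figures are miscalculated.** They are right for 300 analysed patients, and the paragraph mentions loss to follow-up. That allowance is unquantified, does not mention death, and is attached to the R² = 10% statement. The problem is only that 300 is 5% of those enrolled.
- **That routine-data-only participants inflate the 6000.** The Consent section offers that route ("If the patient does not wish to complete questionnaires for the study at this stage"), but nothing says whether they count towards the target or how many are expected.
- **That the cohort is too small.** The target does not rest on EQ-5D power.

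**Conclusion.** The point holds as a correction to stated figures that should be made; it is not a flaw in the design. The EQ-5D sample in the example omits deaths, and the pilot's 88% cannot fill the gap. Which of its two possible definitions the pilot used cannot be settled from the article.

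The example should expect about 227–268 records, not about 300, and its power is about 73–81% (5 degrees of freedom) or 70–78% (6), against 85%. At the favourable end the shortfall is about 4 points with 5 degrees of freedom. The general 95% and 75% figures become about 79–87% and 54–63% when 300 is the number enrolled.

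These ranges rest on three assumptions: mortality at 4 months between 8.5% and 22.5%, 90% response among survivors, and 5 or 6 model degrees of freedom in the example.

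**What to change.** In the Sample size section:

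1. Define the 90% as response among survivors at 4 months, and say how the pilot's 88% treated deaths.
2. Compute the EQ-5D sample as enrolled × proportion alive at 4 months × response among survivors, less any participants who consent to routine data only. State the 4-month mortality assumed.
3. Restate n and power in both the general subgroup paragraph and the subtrochanteric example, giving the model degrees of freedom in the example. Alternatively, keep 85% power and state the detectable effect, about f² = 0.055–0.065 with 5 degrees of freedom.

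The 6000 target, the death-rate table and the R² = 10% statement need no change, and no more patients need be enrolled. An analysis scoring deaths as 0 is optional and belongs in the individual studies' analysis plans. The cost is a recalculation and a few sentences, with less favourable power on the page.

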### Validation

Once the initial sample size of 6000 patients has been achieved, we will use other data sets to externally validate the cohort and determine its generalisability. In particular, we will explore the NHFD, HES and the CPRD to determine whether the WHiTE cohort is truly representative (eg, in terms of age structure) of the wider UK hip fracture population. This should help contextualise WHiTE data before they are used to determine research priorities and inform health policy.

### Dissemination and publication

The results of this study will be disseminated to the hip fracture clinical community via presentations at national and international meetings as well as publication in peer-reviewed journals and social media. Patient reports will also be made available to participants and the wider public via newsletters and podcasts. The results of the observational studies will influence the next generation of hip fracture guidelines, for example the UK NICE Hip Fracture Guidelines, and generate hypotheses that can be tested in interventional study designs.
